**2. Study Design**

**2.1 Study Overview**

The objective of study is to assess the efficacy and safety of electro-acupuncture (EA) for symptoms associated with severe functional constipation.

**2.2 Background**

Constipation is a common gastrointestinal disease. The prevalence of chronic functional constipation is 14.7% in the USA and 11.6% in Asia. Patients with severe chronic constipation have complete spontaneous bowel movements (CSBMs) no more than twice per week, with hard stools, and the frequency of staining is usually more than 1/4. The disorder is so intractable that nearly half of patients are

dissatisfied with their laxative therapies. Despite an instant effect, long-term use of medicine may lead to some side effects such as drug dependence, melanosis coli, laxative-induced constipation, or even cancerization. Systematic reviews indicate that acupuncture might be effective for constipation; however, the evidence is limited. Our pilot studies showed deep needling electro-acupuncture (EA) worked from week 1, which was quicker than either shallow needling (worked from week 2) or medication with lactulose (Duphalac). The treatment group adopted deep needling at Tianshu (ST25), who showed a frequency of weekly spontaneous defecation of  $2.75 \pm 1.48$  ( $M \pm SD$ ), compared with the shallow needling group ( $0.79 \pm 0.93$ ) and the medication group ( $2.17 \pm 1.15$ ) after 4 weeks of treatment. This study indicated that deep needling EA at ST25 might be superior to shallow puncture and Duphalac, but further research is needed to provide more evidence. In addition, these studies had significant limitations which include lack of information about the severity of patients' constipation symptoms at baseline and the assessing endpoints limited to the last week of treatment or follow-up. By comparison, in this trial, patients with severe constipation will be treated for 8 weeks, and followed up for 12 weeks by assessing the mean weekly value of outcomes during the 8-week treatment and 12-week follow-up. In addition, this trial is a multicenter randomized controlled trial, and aims to evaluate the safety and effectiveness of EA for severe constipation.

### **2.3 Study Objectives and Hypothesis**

Study objective is to assess the efficacy and safety of EA, and to test the hypothesis that the efficacy of EA is better than that of sham electro-acupuncture (SA) in patients with chronic severe functional constipation. In addition, the sustained effect of EA will also be evaluated.

Hypothesis:

The group receiving EA treatment will have a statistically significant and clinically important improvement over the group receiving SA.

### **2.4 Methodology**

#### **2.4.1 Trial Design**

This is a 15-site, two-arm, randomized controlled trial, which will be performed from Oct 1, 2012 to Nov 30, 2014 (Figure 1). All the acupuncturists in each site are required to have an official license and clinical work experience no less than 2 years. In this trial, the participants, evaluators, and statisticians will be blinded.

#### **2.4.2 Subjects**

Participants must meet the diagnostic criteria for functional constipation according to Rome III: (1) must include  $\geq 2$  of the following: 1) straining during  $\geq 25\%$  of defecations, 2) lumpy or hard stools in  $\geq 25\%$  of defecations, 3) sensation of incomplete evacuation for  $\geq 25\%$  of defecations, 4) sensation of anorectal obstruction /blockage for  $\geq 25\%$  of defecations, 5) manual maneuvers to facilitate for  $\geq 25\%$  of defecations, 6)  $< 3$  defecations per week; (2) loose stools rarely present without use of laxatives; (3) insufficient evidence for irritable bowel syndrome. To meet the criteria of functional constipation,  $\geq 2$  of these symptoms must have been present for  $\geq 3$  months, with symptoms onset  $\geq 6$  months before diagnosis.

##### **2.4.2.1 Inclusion Criteria**

Participants will be included if they fulfill all of the followings: (1) Meeting the diagnosis of Rome III criteria for chronic functional constipation; (2) Severe chronic constipation with two or fewer complete spontaneous bowel movements (CSBMs) per week for more than 3 months; (3) Aged 18 to 75 years old; (4) No use of medicine for constipation 2 weeks before enrollment (except rescue medication), no acupuncture treatment for constipation in the previous 3 months, and had not joined any other trial in the previous 3 months; (5) Volunteered to join this research and signed the informed consent.

##### **2.4.2.2 Exclusive Criteria**

Participants will be excluded if they met any of the followings: (1) constipation caused by irritable bowel syndrome (IBS), or drugs, or secondary to endocrine, metabolic, nervous or postoperative diseases; (2) Constipation accompanied with serious cardiovascular, hepatic, or renal damage, or with cognitive dysfunction, psychiatric disorder, aphasia, or severe dystrophy, which might affecting the cooperation for examination or treatment; (3) women in gestation or lactation periods; (4) Constipation accompanied with abdominal aneurysm, hepatosplenomegaly; (5) Bleeding disorders, or regular anticoagulant drug users, such as warfarin, heparin, etc.; (6) Cardiac pacemaker carrier.

##### **2.4.2.3 Subject Withdrawals**

The participants may leave the study at their own discretion, or the experts from the gastrointestinal or anorectal department in each site may determine that it is the best for the participants to discontinue participation (due to worsening of symptoms, or the occurrence of a serious adverse event). Members of

our data and safety monitoring board (DSMB) of the trial will take charge of the data monitoring and safety, and will decide if the whole clinical trial should be aborted according to the evaluation of severe adverse effects.

#### **2.4.2.4 Subject Recruitment, Screen and Grouping**

Participants with severe functional constipation will be recruited through posters, or advertisements on newspapers, websites, or on TV. Research assistants of each site will preliminarily screen the participants by recording their disease condition, history of the disease and treatment, and the demographic data.

Physicians from the gastrointestinal or anorectal department of each site will take charge of the diagnosis and the differential diagnosis of the severe functional constipation. Potential participants will fill out a 2-week screening defecation diary to record their bowel movements, constipation-related symptoms, medications, etc. Eligible participants then will be randomized to EA or SA group. Acupuncturists are in charge of the participants' assignment, and the EA or SA manipulation. They are also responsible for the assessment of safety during treatment. Research assistants take care of the diet instruction for the participants, and let them keep the diet and daily routines as usual. They also require the participants to stop their medicine for constipation. During the trial, the professional evaluators of each site will instruct the participants how to fill in their defecation diaries and patients' self-assessment related to the trial and the evaluators will record the data on the case report form (CRF) through the whole trial period.

#### **2.4.3 Flow Chart**

[figure not shown]

**Figure 1 Flow Chart**

#### 2.4.4 Sample Size

According to our pilot study, the weekly CSBMs increase was conservatively estimated at 1.49 times, with a standard deviation of 1.77, after 8 weeks EA treatment; the weekly CSBMs increased by 1.01, with a standard deviation of 1.61, after 8 weeks SA treatment. We used SAS 9.3 to define the 95% power, using a one-way analysis of variance fixed effects omnibus test, assuming a 20% loss to follow-up. To ensure the stratified randomization, the sample size calculation result is 1034.

1034 participants were enough to provide 95% power to detect a difference of 0.5 in the change of weekly CSBMs between the two groups at a significance level of 5% using analysis of variance. The intergroup difference of 0.5 weekly CSBMs was within the range of published estimates of the minimum clinically important difference (MCID) for weekly CSBMs.

#### 2.4.5 Randomization

Participants will be randomized to EA and SA groups with a ratio of 1:1 by using the central stratified block randomization. The site will be set as the stratified factor. The professional biostatisticians will

generate the randomization schedule and related document by using SAS 9.3 software, PROC PLAN. A central randomization system (Institute of Basic Research in Clinical Medicine, China Academy of Chinese Medical Sciences) will be adopted. The researchers who take charge of the randomization will input the birthdate and gender of the eligible subjects through telephone or website to get the random numbers. Experts who will generate the randomization schedule from the Institute of Basic Research in Clinical Medicine, China Academy of Chinese Medical Sciences will take no part in the statistical analysis. The randomization schedule and the related parameters will be sealed and signed by the experts and kept by the staff that doesn't participate in our research. No one has the right to check the randomization schedule.

#### 2.4.6 Blinding

The participants, evaluators, and statisticians will be blinded. Participants do not know which intervention they will be given. The evaluators from each site who is blinded about the assignment will take charge of the outcome assessment. And the statistician who is blinded about assignment from Institute of Basic Research in Clinical Medicine, China Academy of Chinese Medical Sciences will be responsible for the statistical analysis.

#### 2.4.7 Outcomes Measurement

##### 2.4.7.1 Primary Outcome

The change of the mean weekly complete spontaneous bowel movements (CSBMs) from baseline over the 8-week treatment:

$$\frac{\text{the total number of CSBMs over the 8 weeks of treatment}}{8} - \frac{\text{the total number of CSBMs over the 2 weeks of baseline}}{2}$$

Assessing points: baseline, at the end of week 8.

The professional evaluators totalize the CSBMs according to patients' defecation diaries.

##### 2.4.7.2 Secondary Outcomes

- (1) The proportion of patients having  $\geq 3$  CSBMs/week over 8-week treatment, assessing points: baseline, at the end of week 8. The CSBMs/week of the patients with severe constipation are  $\leq 2$  at baseline; therefore, the proportion of patients having  $\geq 3$  CSBMs/week can reveal the clinical effectiveness.
- (2) The proportion of patients having  $\geq 3$  CSBMs/week over 12-week follow-up, assessing points: baseline, at the end of week 20.
- (3) The change of the mean weekly CSBMs from baseline over the 12-week follow-up:

$$\frac{\text{the total number of CSBMs over the 12 weeks of follow-up}}{12} - \frac{\text{the total number of CSBMs over the 2 weeks of baseline}}{2}$$

Assessing points: baseline, at the end of week 20.

- (4) The change of the mean weekly spontaneous bowel movements (SBMs) from baseline over the 8-week treatment:

$$\frac{\text{the total number of SBMs over the 8 weeks of treatment}}{8} - \frac{\text{the total number of SBMs over the 2 weeks of baseline}}{2}$$

Assessing points: baseline, at the end of week 8.

The professional evaluators totalize the SBMs according to patients' defecation diaries.

- (5) The change of the mean score of stool consistency during each SBM from baseline over the 8-week treatment:

$$\frac{\text{sum of the score of stool consistency over the 8 weeks of treatment}}{\text{frequency of SBMs over the 8 weeks of treatment}} - \frac{\text{sum of the score of stool consistency over the 2 weeks of baseline}}{\text{frequency of SBMs over the 2 weeks of baseline}}$$

Assessing points: baseline, at the end of week 8.

Participants will report the stool consistency during their each SBM according to the 7-type BSFS (scored by 1 to 7 respectively).

| Bristol stool form scale |                                                                  |
|--------------------------|------------------------------------------------------------------|
| type de selles           | description                                                      |
| 1                        | selles dures en forme de billes détachées (selles difficiles)    |
| 2                        | selles en forme de billes collées                                |
| 3                        | selles en forme de boudin, structure friable                     |
| 4                        | selles en forme de boudin, structure douce et lisse              |
| 5                        | selles molles avec contours clairement tranchés (selles faciles) |
| 6                        | selles molles à très molles aux contours imprécis                |
| 7                        | selles aqueuses sans structure (totalement liquides)             |

- Type 1: Separate hard lumps, like nuts (hard to pass)
- Type 2: Sausage-shaped, but lumpy
- Type 3: Like a sausage but with cracks on its surface
- Type 4: Like a sausage or snake, smooth and soft
- Type 5: Soft blobs with clear cut edges (passed easily)
- Type 6: Fluffy pieces with ragged edges, a mushy stool
- Type 7: Watery, no solid pieces. Entirely liquid

6) The change of the mean score of straining during each SBM from baseline over the 8-week treatment:

$$\frac{\text{sum of the score of straining of every SBM over the 8 weeks of treatment}}{\text{frequency of SBMs over the 8 weeks of treatment}}$$

$$- \frac{\text{sum of the score of straining of every SBM over the 2 weeks of baseline}}{\text{frequency of SBMs over the 2 weeks of baseline}}$$

Assessing points: baseline, at the end of week 8.

Participants will report the degree of straining during their each SBM in the defecation diaries.

- 0 = not difficult
- 1 = a little difficult, need some straining to defecate
- 2 = difficult, need straining to defecate
- 3 = very difficult, need hard straining to defecate

(7) The change of the score of PAC-QOL from baseline at week 8.

Patient Assessment of Constipation Quality of Life questionnaire (PAC-QOL) is a self-report questionnaire for evaluating the quality of life in participants with constipation, which was distributed by Mapi Research Trust in France. This questionnaire contains 28 items including 4 basic parts of physical discomfort, worries and concerns, psychosocial discomfort, and satisfaction. We will use the Chinese version in our trial.

Assessing points: baseline, at the end of week 4 and week 8.

(8) The proportion of rescue medicine (glycerol enema, or sorbitol enema) used over the 8-week treatment and 12-week follow-up, and the mean weekly frequency of rescue medicine used during the same time frame; the proportion of other assistant methods used for constipation during the same time frame, and the mean weekly frequency of other assistant methods used during the same time frame.

Assessing point: baseline, at week 4, week 8, and week 20.

(9) Subgroup analysis

The subgroup analysis on the primary outcome by stratified the participants as < 65 years and ≥65 years will be conducted.

Assessing points: baseline, at the end of week 8.

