**Figure 2 The study period and assessing timeframe of our trial**

### 4.3 Rescue Medicine

If the participants don't have a bowel movement for 3 or more consecutive days during the whole trial period, they are allowed to use glycerol enema 110ml, or sorbitol enema 40–60ml once into anus as a rescue medicine. The time, frequency, and dosage of the rescue medicine used should be recorded at length on participants' defecating diaries. Other drugs for constipation are not allowed in our trial. However, if the participants have used any other drug, they must faithfully record on their diaries the name, time, frequency, and dosage of the drug used.

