As the main objective is to compare the changed number of weekly average CSBMs throughout the 8 weeks of treatment with the average weekly CSBMs during the 2 weeks baseline period, the primary analysis of the patient-level data is the number of CSBMs per week for 8 weeks. It means the total amount of CSBMs during 8 weeks will be divided by eight to achieve the result. (Each patient therefore has one number of weekly CSBMs throughout the 8 weeks of treatment). The null hypothesis is this number of CSBMs is the same between the EA and SA groups, and the alternative hypothesis is that the change from baseline in CSBMs at 8 weeks for the EA group does not equal the SA group. The subjects who do not receive any treatment after randomization or receive treatment but not any efficacy assessment data are classed as missing data, and multiple imputation methods will be used to deal with the missing data. An analysis of covariance (ANCOVA) will be used group, study site and baseline CSBMs will be included in the ANCOVA model. The secondary outcome measures include the following seven items: 1) the proportion of participants with three or more mean weekly CSBMs during weeks 1–8 and weeks 9–20; 2) the change from baseline in mean weekly CSBMs during weeks 9–20; 3) the change from baseline in mean weekly spontaneous bowel movements (SBMs); 4) the change from baseline in mean stool consistency over weeks 1–8; 5) the change from baseline in mean straining scores over weeks 1–8; 6) the change from baseline in PAC-QOL scores at week 8; 7) the proportion and mean weekly frequency of rescue medicine and other defecation assistances used. Chi-square test was used to compare the proportion of participants having three or more CSBMs and the proportion of other rescue medicine and other defecation assistances used between two groups. Student's t test was used to compare the change from baseline of mean weekly SBMs and the scores in PAC-QOL, stool consistency, and straining between groups. Wilcoxon rank sum test was used to compare the mean weekly frequency of other rescue medicine and other defecation assistances used between groups. Subgroup analysis will be conducted according to the subject's age (<65 years and ≥65 years). All adverse events and serious adverse events will be listed. Poisson regression model will be used to compare the incidence of adverse events between the EA and SA groups.

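### The stool-consistency and straining change scores are undefined for a participant with no SBM at baseline (or on treatment), and the protocol does not say how such a participant is analysed

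*Protocol*

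**What the plan says.** Protocol section 2.4.7.2 prints a formula for each outcome. Outcome (5), stool consistency, divides the summed Bristol scores by the "frequency of SBMs over the 8 weeks of treatment" and subtracts the corresponding baseline ratio, whose denominator is the "frequency of SBMs over the 2 weeks of baseline". Outcome (6), straining, is built the same way; its baseline numerator is the "sum of the score of straining of every SBM over the 2 weeks of baseline". Neither formula has a rule for a zero count.

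Four other places bear on whether the count can be zero:

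- Section 2.4.2.1 requires "Severe chronic constipation with two or fewer complete spontaneous bowel movements (CSBMs) per week for more than 3 months". This is an upper limit on complete SBMs; there is no lower limit on SBMs.
- The same section asks for "No use of medicine for constipation 2 weeks before enrollment (except rescue medication", so rescue use in the 2 weeks before enrolment does not disqualify.
- Section 4.3 allows a rescue enema when there has been no bowel movement "for 3 or more consecutive days during the whole trial period", and section 4.2 counts the 2-week screening within the 22-week trial.
- The outcome definitions that follow section 2.4.7.2 class any bowel movement within 24 hours of rescue or another assisting method as non-spontaneous.

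On analysis, section 8.3 states: "Student's t test was used to compare the change from baseline of mean weekly SBMs and the scores in PAC-QOL, stool consistency, and straining". Section 8.2 keeps every randomised participant and sends missing data to multiple imputation. Section 8.3, in its text on the primary analysis, classes as missing those with no treatment or with no efficacy data at all. A ratio that cannot be formed is not mentioned.

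**The concern.** An endpoint defined by a printed formula should have a value for every eligible participant, or a stated rule where it has none. Here the formula divides by something the participant may not have produced.

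The analyst then has two routes, both poor. Leaving the participant out of the t test departs from the all-randomised population and loses someone whose on-treatment scores may be fully recorded. That includes a participant who had no SBM at baseline and begins to have them during treatment. Imputing the baseline term treats a stool form and a straining score as missing when the stool never happened. If the choice is made after the data are seen, it is open to selection.

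The denominator over weeks 1 to 8 has the same weakness. A zero there is much rarer, but it arises after randomisation and so could differ between arms.

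**Working it through.** **1. Which endpoints are exposed.** The primary outcome and outcomes (3) and (4) divide by a fixed number of weeks (2, 8 or 12), so a zero count simply gives a mean of zero. Only outcomes (5) and (6) divide by the participant's own SBM count.

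**2. Can an eligible participant have no baseline SBM?** Take a 14-day screening diary with no bowel movement on days 1–3, 5–7, 9–11 and 13–14, and an enema followed by defecation the same day on days 4, 8 and 12. Three bowel movements are recorded, all within 24 hours of rescue. SBMs = 0 and CSBMs = 0 per week, which satisfies the limit of two. Summed score = 0 and SBM count = 0, so the baseline term is 0/0 and the change score does not exist, whatever is recorded in weeks 1 to 8.

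**3. How many?** The protocol states no figure for this and gives no baseline SBM rate, so there is nothing to reproduce and the share has to be assumed. For Poisson counts at rate r per week, P(no SBM in 2 weeks) = exp(−2r). The planned 1034 is used only to scale.

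| Assumed SBMs per week | P(none in 2 weeks) | Of 1034 |
|---|---|---|
| 0.5 | exp(−1.0) = 36.8% | 380 |
| 0.79 | exp(−1.58) = 20.6% | 213 |
| 1 | exp(−2) = 13.5% | 140 |
| 1.5 | exp(−3) = 5.0% | 51 |
| 2 | exp(−4) = 1.8% | 19 |
| 3 | exp(−6) = 0.25% | 3 |

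The rate 0.79 (SD 0.93) is the only low spontaneous frequency in the document. Section 2.2 reports it for the pilot arm against which deep needling was "compared with the shallow needling group", after 4 weeks of treatment. It is not a baseline value and not from this trial.

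**4. Variation between patients.** If patients differ in their underlying rate (negative binomial with shape k), P(none in 2 weeks) = (k/(k + 2r))^k.

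- Matched to the pilot mean and SD: k = 0.79²/(0.93² − 0.79) = 0.6241/0.0749 ≈ 8.3, giving 23.5%, about 243 of 1034.
- Strong variation, k = 1: 1/(1 + 4) = 20% at 2 per week and 1/(1 + 6) = 14% at 3 per week.

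A higher mean rate therefore does not by itself make the problem negligible.

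**5. No SBM in the 8 treatment weeks.** Poisson: exp(−8 × 0.79) = 0.18%, about 2 of 1034; exp(−8 × 0.5) = 1.8%. Negative binomial with k = 8.3 at 0.79 per week: 0.9%, about 9 of 1034.

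**The case against.** Four arguments weigh against making much of this.

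*It is detail for the SAP.* Derivation rules for diary endpoints are often left there, and the SAP is not at hand. But the protocol prints these formulas itself, and as printed they have no value for some eligible participants. A SAP may repair that; the text that needs the repair is in the protocol.

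*A reader might infer that these participants drop out, so that the two endpoints describe only the milder patients.* The document does not say so. Section 8.2 keeps all randomised participants and provides for multiple imputation, and the cases section 8.3 names as missing do not include an undefined ratio. What stands is that handling is unspecified and that neither available route is sound.

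*A reader might take one fifth of the trial as the expected loss.* The documents do not support that either. The 0.79 per week is a post-treatment pilot figure. Eligibility caps complete SBMs only, and incomplete ones count as SBMs, so a participant with three or more incomplete SBMs per week can qualify. The share could be well under 1%. That some baseline counts will be zero is a plausible inference, not a documented fact.

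*A reader might infer bias between arms.* For baseline zeros this does not follow, because they are fixed before randomisation. Zeros over the 8 treatment weeks could be unbalanced, but they are rare at the rates considered, and saying they would be commoner under sham presumes that the treatment works. The affected participants also count fully in the primary outcome and in SBM change, outcome (4).

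**Conclusion.** The point holds in a limited form. Outcomes (5) and (6) are undefined for any participant with no SBM in the 2 baseline weeks or, rarely, in the 8 treatment weeks. Eligibility permits this, and the protocol does not settle whether such a participant is left out or imputed.

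The size cannot be fixed from the document. Over assumed rates of 0.5 to 3 SBMs per week, the Poisson share with no baseline SBM runs from 36.8% down to 0.25%, and it is higher where patients vary strongly. These figures rest on the assumed rates and on the count model.

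The cost is lost precision and weaker applicability to the most severe patients on two secondary endpoints. Baseline zeros do not bias the comparison between arms, and the primary outcome is untouched. It is still worth settling before unblinding, because the remedy is cheap and uses data already collected.

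**What to change.** For outcomes (5) and (6), replace the t test on change by an ANCOVA of the 8-week mean score with terms for group, study site, baseline mean score and an indicator for no baseline SBM, setting the baseline score to a constant where the indicator is on. Because the indicator is fixed before randomisation, it keeps these participants in without disturbing the comparison. The model is close to the ANCOVA that section 8.3 already plans for the primary outcome.

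State that scores are not imputed where the diary shows that no SBM occurred; imputation stays for diary data that are truly missing. Report by arm the number with no on-treatment SBM. A sensitivity analysis giving those participants the worst score (straining 3, Bristol type 1) is optional. It is a bounding exercise, since those scores do not exist either.

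The cost is rewording two endpoint definitions and one sentence of the analysis section, with no new data. The small downside is that the estimate becomes a difference in adjusted 8-week means rather than in raw change scores. It also applies to participants with at least one on-treatment SBM, which is a selection made after randomisation; the count by arm shows whether that matters.
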